#### Safety assessment and risk prevention

To mitigate risk of injury, in addition to experiencing a familiarisation protocol (Fig 1) participants will be required to wear their usual running/sport shoes. Risk of falling will also be mitigated by the unloading harness being attached to the pelvis and shoulders. Participants will also be instructed to report any discomfort experienced to allow mitigation via rest and/or harness adjustment.

#### L.O.O.P. facility

The L.O.O.P. facility is located within the cavaedium, a square (3 x 3 m) but tall (17 m) (Fig 2) space inside the Human Physiology building of the University of Milan where calibrated bungee cords provide body suspension [15, 16, 47], compatible with a double split-belt instrumented treadmill (Bertec, USA) provided by the German Aerospace Center (DLR) (see “*Study Hardware”* for treadmill specifications). The body suspension system consists of two bungee cords (Exploring Outdoor srl, Italy) with a resting length of 4 m and a stiffness of 92.7 N·m^-1^. The bungee cords are linked in-series with an inextensible short cable (Dyneema SK78, diameter 4 mm, length 1.2 m, Gottifredi & Maffioli, Italy), working on an upper pulley. One of the bungee cords is fixed to the wall, while the other is connected to a force transducer (TS 300kg, AEP Transducers, Italy) placed in series with a body harness. The upper pulley can be raised or lowered by means of a suspension cable which is connected to a motorized winch (2.20 kW, Officine Iori SRL, Italy) allowing the titration (determined by the force transducer) of body (harness) unloading to the required gravity level (present study: 1, 0.7, 0.5, 0.38, 0.27, and 0.16g).

**Fig 2 pone.0278051.g002:**
[figure not shown]
L.O.O.P. facility. *Left*: Picture of the cavaedium wherein the L.O.O.P has been installed, showing the two bungee cords, the inextensible short cable linking both bungee cords, and several of the motion analysis cameras. *Right*: Schematic of the experimental setup showing a participant in the harness connected to the bungee cords, walking on the treadmill in the middle of the capture environment and equipped with the EMG-sensors, reflective markers, and ultrasound probe.

A key advantage of the L.O.O.P. compared to other hypogravity simulators results from the fact that the upper pulley is located high above the participant (~16 m), any horizontal forces generated due to fore-aft and/or lateral displacements during locomotion on the treadmill are minimised. For example, at 0.16g, a horizontal movement of 0.03 m with respect to the pulley results in an additional horizontal force of 0.92 N, representing just 0.4–0.7% of the peak push-off force during terrestrial (1g) stance [50]. Furthermore, the height of the shaft allows the use of a single pulley to accommodate the 20 m (when extended, 2 x 10 m) bungee cords limiting friction and displacement, independent of vertical force [15]. However, although high-fidelity simulated hypogravity is provided by generation of near constant vertical forces to the body’s centre of mass (BCoM), swinging limbs remain subject to 1g –and thus can generate pendulum-like effects if exaggerated motion is performed. Thus, participants will be instructed to consider limb motion as stabiliser activity during jumping.

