### Planned statistical analysis

Statistical significance will be assumed at p < 0.05. Normality of the data will be assessed via Kolmogorov-Smirnov testing complemented by visual inspection of QQ plots and histograms. Normally distributed data will be presented as mean (±SD), non-normally distributed data will be presented as median (±IQR).

The effect of high-fidelity simulated gravity (1, 0.7, 0.5, 0.38, 0.27 and 0.16g) upon lower limb internal kinetics (i.e., joint reaction forces) when walking, running, and skipping at speeds ranging between 0.53–3.6 m/s will be determined by a Two-Way Repeated Measures ANOVA with:

Independent variables: six simulated gravity conditions; 10 locomotion trials (see Table 1)Dependent variables: Joint reaction forces of the hip, knee, and ankle

The effect of high-fidelity simulated gravity (1, 0.7, 0.5, 0.38, 0.27 and 0.16g) upon lower limb internal kinetics (i.e., joint reaction forces) during candidate plyometric movement (i.e., maximal ankle hopping, maximal effort countermovement jumping, and drop-jumps/landings) will be determined by a One-Way Repeated Measures ANOVA with:

Independent variables: six simulated gravity conditionsDependent variables: Joint reaction forces of the hip, knee and ankle

In case the assumption of sphericity has been violated–i.e., Mauchly’s test statistic is significant (p<0.05)–the Geisser-Greenhouse correction will be used to determine the effect of the independent variables on the dependent variables. If a significant effect of the simulated gravity condition, the locomotion trial, or the interaction between simulated gravity condition and locomotion trial is found, Bonferroni corrected post-hoc t-tests will be employed.

Alternatively, if data has a non-normal distribution the non-parametric Friedman test with Dunn’s post-test will be used.

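### Near-constant vertical support holds for locomotion but not for maximal jumps at the lowest gravity levels, where flight takes place well above the labelled gravity

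*Protocol article*

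**What the plan says.** The L.O.O.P. facility section describes two bungee cords "with a resting length of 4 m and a stiffness of 92.7 N·m^-1". It adds: "The bungee cords are linked in-series with an inextensible short cable", which runs over an upper pulley. A motorised winch sets the pulley height until an in-series force transducer shows the unloading required for the chosen level. The text after Fig 2 says that the tall shaft lets a single pulley "accommodate the 20 m (when extended, 2 x 10 m) bungee cords", and credits the system with "generation of near constant vertical forces to the body"'s centre of mass. The only error it works out is horizontal: at 0.16g, "a horizontal movement of 0.03 m with respect to the pulley results in an additional horizontal force of 0.92 N". It gives no figure for vertical change.

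The Introduction presents L.O.O.P. as, to the authors' knowledge, the only ground-based analogue in which maximal jumping can be evaluated. Table 4 lists flight time as an outcome for plyometric trials, and the 3D-Motion analysis section derives vertical displacement in maximal countermovement jumps. The simulated plyometric cycle comprises one contact and the flight that follows it (Planned data analysis). Support forces are listed as external loads in the Fig 3 caption and the Optimal control framework section, without saying whether they vary in time. The statistical analysis takes the six nominal levels as the factor for joint reaction forces "during candidate plyometric movement (i.e., maximal ankle hopping, maximal effort countermovement jumping, and drop-jumps/landings").

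**The concern.** An elastic cord loses tension as the jumper rises. At 0.16g it carries 84% of body weight, so a moderate fractional loss of support is a large fractional gain in the small remainder that acts as gravity. Jumps are also highest at this level. The protocol's reassurance rests on cord length and a horizontal example, neither of which tests a rise of one to two metres.

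At stake is what the label 0.16g means for a jump. Flight time and jump displacement at the lowest levels would describe a gravity that increases with height, by an amount that differs with body mass and jumping ability, yet would be reported as Lunar values. If a constant nominal support force were entered in the simulation, the flight part of the cycle would carry a force error that dynamic consistency cannot show as a pelvis residual, because those residuals are set to zero.

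**Working it through.** **Inputs from the protocol:** resting length 4 m, stiffness 92.7 N/m, two cords in series, extended length 2 x 10 m, pulley about 16 m above the participant, 0.92 N at 0.03 m, lowest level 0.16g.

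**Assumptions (not in the protocol):** body mass 60–80 kg, 1g jump height H of 0.20–0.50 m, take-off speed unchanged from 1g, linear lossless cords, pulley height fixed during a jump, g = 9.81 m/s².

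**1. Does 92.7 N/m refer to each cord?** The protocol does not say. Length per cord at 0.16g = 4 + 0.84·m·g/92.7. For 70 kg the tension is 0.84 × 70 × 9.81 = 577 N and the length 4 + 577/92.7 = 10.2 m. At 60 and 80 kg it is 9.3 and 11.1 m, and exactly 10.0 m at 67.5 kg. This reproduces the stated 10 m. If 92.7 N/m were the whole-system value, each cord would reach only 6.7–7.6 m at 60–80 kg. The per-cord reading fits.

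The horizontal example is consistent with a plausible load: T × 0.03/16 = 0.92 N gives T = 491 N, which is 0.84g of unloading for 59.5 kg.

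**2. Loss of support per metre.** Series stiffness k = 92.7/2 = 46.35 N/m. At 70 kg this is 46.35/(70 × 9.81) = 0.068g per metre.

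**3. Locomotion.** A vertical excursion of ±0.05 m (assumed) changes gravity by ±0.003–0.004g at 60–80 kg.

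**4. One maximal jump at 0.16g: 70 kg, take-off 2.8 m/s** (H = 2.8²/(2 × 9.81) = 0.40 m).
- Rise x solves v²/2 = 0.16g·x + (k/2m)x², that is 3.92 = 1.570x + 0.331x², so x = 1.81 m. With constant support it would be 0.40/0.16 = 2.50 m.
- Apex gravity = 0.16 + 46.35 × 1.81/(70 × 9.81) = 0.28g. Support has fallen by 84 N of 577 N, about 15%.
- Flight time = (2/ω)·arctan(vω/0.16g), with ω = √(k/m) = 0.814 per second: (2/0.814) × arctan(1.45) = 2.4 s. With constant support it would be 2 × 2.8/1.570 = 3.6 s.

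**5. Range at nominal 0.16g, apex gravity (rise in metres):**

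| Mass | H = 0.20 m | H = 0.35 m | H = 0.50 m |
|---|---|---|---|
| 60 kg | 0.239g (1.00) | 0.284g (1.58) | 0.323g (2.07) |
| 70 kg | 0.229g (1.03) | 0.270g (1.63) | 0.305g (2.15) |
| 80 kg | 0.222g (1.05) | 0.259g (1.67) | 0.291g (2.22) |

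The range is 0.22–0.32g. On the whole-system reading of the stiffness it would be 0.27–0.43g, so the reading used here is the more lenient one.

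**6. Other levels (70 kg, H = 0.35 m), nominal to apex:** 0.70 to 0.73g, 0.50 to 0.55g, 0.38 to 0.44g, 0.27 to 0.35g, 0.16 to 0.27g. The relative shift is largest at the lowest level.

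**7. Ground contact at 0.16g, 70 kg.** A 0.3 m countermovement (assumed) adds 14 N of support and gives 0.140g. A 0.1 m heel rise gives 0.167g. At 0.35 m depth the change is 16 N, or 0.024g. Reaching 2.8 m/s over an assumed push-off of 0.35–0.40 m needs a mean net force of 70 × 3.92/0.40 = 686 N to 70 × 3.92/0.35 = 784 N. Adding 0.16 × 70 × 9.81 = 110 N, the mean ground force is about 800–890 N, and 16 N is about 2% of that.

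**The case against.** The case on the other side is substantial, and most of it stands.

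- *A reader might infer that the protocol contradicts itself.* It gives no tolerance for its near-constant wording, and the Introduction says only that long cords minimise the change in recoil. The support force itself falls by 7–19% over the range above. The claim is unsupported for high jumps at the lowest levels; it is not contradicted.
- *A reader might take 0.28g as the result.* The protocol gives no body mass, jump height or take-off speed. Only the range, with its assumptions, can be defended.
- *A reader might infer that the primary outcome is compromised.* The apex has no ground contact. In contact the shift is about 0.02g. An elastic cord returns energy, so landing speed at take-off height is about take-off speed. In a drop from an assumed 0.3 m at 70 kg, impact speed is 1.00 rather than 0.97 m/s.
- *A reader might infer confounding by body mass.* Every participant performs all six levels and the ANOVA is repeated-measures. Mass is constant within a participant and cannot confound the gravity contrast; it can only alter its size.
- *A reader might infer that 0.16g jumps become the 0.27g condition.* Apex gravity also rises in that condition, to 0.35g in the same example, and the order of the levels is kept.
- *A reader might infer that support force is ignored or measured only beforehand.* Support forces are already model inputs, and the text does not restrict the transducer to use before a trial. Whether the signal is logged throughout is detail that an article may leave to the full protocol.

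What the objection does not remove is that flight time and jump displacement are stated outcomes, that flight belongs to the simulated cycle, and that maximal jumping is the facility's claimed distinction.

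**Conclusion.** The point holds in a limited form. On the protocol's own stiffness and layout, near-constant support is justified for locomotion (under 0.01g) but not for maximal jumps at the lowest levels. Even the mildest case in the range, 0.22g, is more than a third above the 0.16g label. In the worked example the jump is 28% lower (1.81/2.50 = 0.72) and the flight about a third shorter (2.4/3.6 = 0.67).

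The consequence lies in flight time, jump displacement and the meaning of the gravity label, not in peak joint reaction forces or the validity of the within-participant comparison. The conclusion rests on the per-cord reading of 92.7 N/m, on linear cords, and on the assumed masses and take-off speeds. The size would change with these; the direction would not. It is worth correcting before data collection, because a support-force signal that was not recorded cannot be recovered directly.

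**What to change.** 1. State that 92.7 N/m is the stiffness of each cord, if so, and give the vertical change: about 46 N per metre of rise for the two in series.
2. Record the in-series transducer, synchronised, in every trial, and state that its time-varying signal is the body weight support force used in the tracking simulations and the joint reaction analysis.
3. Report achieved gravity for each plyometric trial, as the contact-phase mean and the value at the apex.
4. Keep the nominal-level repeated-measures ANOVA as the primary analysis. Add achieved contact-phase gravity as a sensitivity analysis only: it depends on movement depth and effort, which themselves respond to the condition, so as the main regressor it would bring its own bias.
5. Limit the near-constant and high-fidelity wording to locomotion and ground contact, and give the achieved range for jumps.

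The cost is one extra synchronised channel from a transducer already installed, one sensitivity analysis, and a slightly less favourable statement of fidelity. No new hardware or change of design is needed.

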### Study hardware

#### Treadmill

A double split-belt instrumented treadmill (total walking surface: 1.75 x 1m; speed: 0–5.83 m/s; Bertec, USA) will record 6-component loads from each belt (Fx, Fy, Fz, Mx, My, Mz) at a sampling rate of 2000 Hz which will be integrated into the 3D-Motion Capture System.

#### 3D-Motion analysis system

The L.O.O.P. is equipped with a 3D Motion Capture System (Vicon Motion Systems Ltd, UK) consisting of 24 cameras (Vicon MX Cameras, Vicon Motion System Ltd., UK) recording marker position at a frequency of 250 Hz, allowing full body segment tracking with a 66 marker set placed on anatomical landmarks according to the calibrated anatomical system technique [51] as described in Table 2 from which BCoM during locomotion, and the vertical displacement associated with maximal effort countermovement jumping are derived.

**Table 2 pone.0278051.t002:** Description of marker locations used for the 3D-Motion analysis.

Segment	Static Markers	Dynamic Markers
*Pelvis*	Right Anterior Superior Iliac Spine Left Anterior Superior Iliac Spine Right Posterior Superior Iliac Spine Left Posterior Superior Iliac Spine	Right Anterior Superior Iliac Spine Left Anterior Superior Iliac Spine Right Posterior Superior Iliac Spine Left Posterior Superior Iliac Spine
*Right Femur*	Right Greater Trochanter Right Lateral Femoral Epicondyle Right Medial Femoral Epicondyle Four-Marker Cluster	Right Lateral Femoral Epicondyle Four-marker cluster
*Right Tibia-Fibular*	Right Lateral Malleolus Right Medial Malleolus Four-Marker Cluster	Right Lateral Malleolus Four-Marker Cluster
*Right Foot Complex (Calcaneus*, *Talus*, *Toes)*	Right Posterior Calcaneus Right Medial MTP5 Right Lateral MTP1 Right Superior MTP2	Right Posterior Calcaneus Right Medial MTP5 Right Lateral MTP1 Right Superior MTP2
*Left Femur*	Left Greater Trochanter Left Lateral Femoral Epicondyle Left Medial Femoral Epicondyle Four-Marker Cluster	Left Lateral Femoral Epicondyle Four-marker cluster
*Left Tibia-Fibular*	Left Lateral Malleolus Left Medial Malleolus Four-Marker Cluster	Left Lateral Malleolus Four-Marker Cluster
*Left Foot Complex (Calcaneus*, *Talus*, *Toes)*	Left Posterior Calcaneus Left Medial MTP5 Left Lateral MTP1 Left Superior MTP2	Left Posterior Calcaneus Left Medial MTP5 Left Lateral MTP1 Left Superior MTP2
*Torso*	Sternum C7 Right Acromion Process Left Acromion Process	Sternum C7 Right Acromion Process Left Acromion Process
*Right Humerus*	Right Lateral Humeral Epicondyle Right Medial Humeral Epicondyle Four-Marker Cluster	Right Lateral Humeral Epicondyle Four-Marker Cluster
*Right Radius-Ulna*	Right Radial Styloid Process Right Ulna Styloid Process Four-Marker Cluster	Right Radial Styloid Process Right Ulna Styloid Process Four-Marker Cluster
*Left Humerus*	Left Lateral Humeral Epicondyle Left Medial Humeral Epicondyle Four-Marker Cluster	Left Lateral Humeral Epicondyle Four-Marker Cluster
*Left Radius-Ulna*	Left Radial Styloid Process Left Ulna Styloid Process Four-Marker Cluster	Left Radial Styloid Process Left Ulna Styloid Process Four-Marker Cluster
*Hands*	No Markers (Locked Wrist Joint)	No Markers (Locked Wrist Joint)

#### Wireless surface electromyography

Sixteen wireless electromyography (EMG) sensors (Trigno, Delsys, USA) will be positioned according to SENIAM guidelines [52] to assess the bilateral myoelectrical activity of m. gluteus maximus, m. rectus femoris, m. vastus lateralis, m. biceps femoris (lateral hamstrings), m. semitendinosus (medial hamstrings), m. tibialis anterior, m. gastrocnemius and m. soleus. Prior to electrode placement each recording area will be shaved, abraded, and cleaned with an alcohol wipe/swab. Electrodes will be secured in place by medical tape (Leukoplast 2.5 cm x 5 m, BSN medical GmbH, Germany). EMG signals will be high-pass filtered, full-wave rectified, and low-pass filtered using a zero-lag second-order Butterworth filter. EMG amplitude will be normalised to each participant’s maximum activation, defined as the maximum value recorded across the 1g dynamic trials for each muscle.

#### Ultrasonography

Real-time B-mode ultrasound using a linear array transducer placed in a custom-made cast and secured with elastic bandages will be positioned over both the m. gastrocnemius medialis mid-belly to determine fascicle length and pennation angles [28, 53], and over the myotendinous junction (MTJ) to determine tendon length [54, 55]. The ultrasound recordings will be time-synchronized with the other data acquisition systems through a TTL pulse passed through the auxiliary ECG channel. A semi-automated tracking algorithm (e.g., UltraTrack Software [56]) will be used to quantify the muscle fascicle length and pennation angles during the stance phase as previously used by our team [57, 58]. For the determination of tendon length, three markers are attached to the ultrasound transducer, enabling the transformation of the tracked fascicle insertion point close to the MTJ in the 2D ultrasound image into the global reference system. Additionally, the m. gastrocnemius medialis tendon length, fascicle length and pennation angle are determined while subjects are lying prone with the knee and ankle joints in anatomically neutral positions (knee fully extended, sole perpendicular to the tibia) and muscles are relaxed [53].

Table 3 provides a comprehensive overview of all equipment used for each part of the experimental sessions.

**Table 3 pone.0278051.t003:** Description of the needed equipment and time for each part of the experimental sessions.

	Familiarisation (*T*_*0*_*)*		Data Collection (*T*_*1*_*)*	
*Activity*—Equipment		Time (Hours)		Time (Hours)
*Laboratory preparation*				
Treadmill	X	0.50	X	0.50
L.O.O.P. Body Weight Support System	X	0.25	X	0.25
Ultrasonography System			X	0.50
EMG System			X	0.25
3D Motion Capture System			X	1.50
*Participant Preparation*				
Body Weight Support Harness	X	0.50	X	0.25
Ultrasonography Probe Placement			X	0.50
EMG Placement			X	0.50
Retroreflective Marker Placement			X	0.50
*Familiarisation Trials*				
L.O.O.P. Body Weight Support System	X	0.50		
*Calibration Trials*				
Ultrasonography System			X	0.25
EMG System			X	0.25
3D Motion Capture System			X	0.25
*Locomotion Trials*				
Treadmill			X	2.50 hours (Based on 1 min trial + 1 min rest + room for additional rest x 6 gravity levels)
L.O.O.P. Body Weight Support System			X	
Ultrasonography System			X	
EMG System			X	
3D Motion Capture System			X	
*Plyometric Trials*				
Treadmill			X	2.50 hours (Based on 3 min trial + 3 min rest + room for additional rest x 6 gravity levels)
L.O.O.P. Body Weight Support System			X	
Ultrasonography System			X	
EMG System			X	
3D Motion Capture System			X	

### Outcome measures

#### Anthropometrics

For each participant, age (years), body mass (kg), -height (m) and leg length (m) will be collected (Table 4).

**Table 4 pone.0278051.t004:** Overview of the anthropometrics, primary and secondary outcome measures to be collected.

Outcome		Unit	Study Hardware	Data Analysis Tool/Software	Data Analysis Procedure
*Anthropometrics*					
Age		Years	n.a.	n.a.	Manual
Body Mass		Kilograms (kg)	Instrumented Treadmill	n.a.	Manual
Body Height		Meter (m)	Stadiometer	n.a.	Manual
Leg Length		Meter (m)	Tape measure	n.a.	Manual
*Primary Outcome Measures–Lower Limb Joint Reaction Forces*					
Hip Joint Reaction Forces		Newton (N)	n.a.	Optimal Control Framework	Automated
Knee Joint Reaction Forces		Newton (N)	n.a.	Optimal Control Framework	Automated
Ankle Joint Reaction Forces		Newton (N)	n.a.	Optimal Control Framework	Automated
*Secondary Outcome Measures–Experimental Data*					
Kinetics	Ground Reaction Forces	Newton (N)	Instrumented Treadmill	Vicon Nexus	Automated
	Net Hip Joint Forces	Newton (N)	3D-Motion Capture System & Instrumented Treadmill	Inverse Dynamics—OpenSim	Semi- Automated
	Net Knee Joint Forces	Newton (N)	3D-Motion Capture System & Instrumented Treadmill	Inverse Dynamics—OpenSim	Semi- Automated
	Net Ankle Joint Forces	Newton (N)	3D-Motion Capture System & Instrumented Treadmill	Inverse Dynamics—OpenSim	Semi- Automated
	Net Hip Joint Moment	Newton Meter (N·m)	3D-Motion Capture System & Instrumented Treadmill	Inverse Dynamics—OpenSim	Semi- Automated
	Net Knee Joint Moment	Newton Meter (N·m)	3D-Motion Capture System & Instrumented Treadmill	Inverse Dynamics—OpenSim	Semi- Automated
	Net Ankle Joint Moment	Newton Meter (N·m)	3D-Motion Capture System & Instrumented Treadmill	Inverse Dynamics—OpenSim	Semi- Automated
Kinematics	Single Support Phase	Percentage gait cycle (%)	3D-Motion Capture System & Instrumented Treadmill	Vicon Nexus	Semi- Automated
	Double Support Phase	Percentage gait cycle (%)	3D-Motion Capture System & Instrumented Treadmill	Vicon Nexus	Semi- Automated
	Stride Frequency	Hertz (Hz)	3D-Motion Capture System & Instrumented Treadmill	Vicon Nexus	Semi- Automated
	Stride Length	Meter (m)	3D-Motion Capture System & Instrumented Treadmill	Vicon Nexus	Semi- Automated
	Flight Time*	Seconds (s)	3D-Motion Capture System & Instrumented Treadmill	Vicon Nexus	Semi- Automated
	Contact Time*	Seconds (s)	3D-Motion Capture System & Instrumented Treadmill	Vicon Nexus	Semi- Automated
	Hip Joint Angle	Degrees (°)	3D-Motion Capture System & Instrumented Treadmill	Inverse Dynamics—OpenSim	Semi- Automated
	Knee Joint Angle	Degrees (°)	3D-Motion Capture System & Instrumented Treadmill	Inverse Dynamics—OpenSim	Semi- Automated
	Ankle Joint Angle	Degrees (°)	3D-Motion Capture System & Instrumented Treadmill	Inverse Dynamics—OpenSim	Semi- Automated
	Hip Joint Angular Velocity	Degrees per Second (°·s^-1^)	3D-Motion Capture System & Instrumented Treadmill	Inverse Dynamics—OpenSim	Semi- Automated
	Knee Joint Angular Velocity	Degrees per Second (°·s^-1^)	3D-Motion Capture System & Instrumented Treadmill	Inverse Dynamics—OpenSim	Semi- Automated
	Ankle Joint Angular Velocity	Degrees per Second (°·s^-1^)	3D-Motion Capture System & Instrumented Treadmill	Inverse Dynamics—OpenSim	Semi- Automated
	M. Gastrocnemius Medialis MTU Activation	n.a.	n.a.	Optimal Control Framework	Automated
Muscle-Tendon Unit Geometries	M. Gastrocnemius Medialis Muscle Length	Millimetres (mm)	n.a.	Optimal Control Framework	Automated
	M. Gastrocnemius Medialis Pennation Angle	Degrees (°)	n.a.	Optimal Control Framework	Automated
	M. Gastrocnemius Medialis Tendon Length	Millimetres (mm)	n.a.	Optimal Control Framework	Automated
Muscle-Tendon Unit Forces	M. Gastrocnemius Medialis Muscle Force	Newton (N)	n.a.	Optimal Control Framework	Automated
	M. Gastrocnemius Medialis Tendon Force	Newton (N)	n.a.	Optimal Control Framework	Automated
Muscle Contraction Dynamics	M. Gastrocnemius Medialis Fascicle Length	Millimetres (mm)	Ultrasonography	MyoResearch software & UltraTrack Software	Semi-Automated
	M. Gastrocnemius Medialis Fascicle Velocity	Millimetres per Second (mm·s^-1^)	Ultrasonography	MyoResearch software & UltraTrack Software	Semi-Automated
	M. Gastrocnemius Medialis Pennation Angle	Degrees (°)	Ultrasonography	MyoResearch software & UltraTrack Software	Semi-Automated
	M. Triceps Surae Tendon Strain	Millimetres (mm)	Ultrasonography	MyoResearch software & UltraTrack Software	Semi-Automated
Muscle Activation Dynamics	M. Gluteus Maximus Activity	Amplitude (mV)	Wireless Surface Electromyography	Delsys EMGworks Software	Automated
	M. Rectus Femoris Activity	Amplitude (mV)	Wireless Surface Electromyography	Delsys EMGworks Software	Automated
	M. Vastus Lateralis Activity	Amplitude (mV)	Wireless Surface Electromyography	Delsys EMGworks Software	Automated
	M. Biceps Femoris Activity	Amplitude (mV)	Wireless Surface Electromyography	Delsys EMGworks Software	Automated
	M. Semitendinosus Activity	Amplitude (mV)	Wireless Surface Electromyography	Delsys EMGworks Software	Automated
	M. Tibialis Anterior Activity	Amplitude (mV)	Wireless Surface Electromyography	Delsys EMGworks Software	Automated
	M. Gastrocnemius Activity	Amplitude (mV)	Wireless Surface Electromyography	Delsys EMGworks Software	Automated
	M. Soleus Activity	Amplitude (mV)	Wireless Surface Electromyography	Delsys EMGworks Software	Automated

*Running, skipping and plyometric trials only.

